**Secondary outcomes**						
	**Anxiety**					
		GAD caseness	GAD-Q-IV (scored categorically)	X	X	X
		Emotional distress from anxiety	PROMIS Emotional Distress from Anxiety measure	X	X	X
		Worry	Penn State Worry Questionnaire (PSWQ)	X	X	X
		Panic disorder symptoms	Panic Disorder Self-Report (PDSR)	X	X	X
		Social anxiety symptoms	Social Phobia Diagnostic Questionnaire (SPDQ)	X	X	X
		PTSD symptoms	Post-Traumatic Stress Disorder Checklist for DSM-V (PCL5)	X	X	X
		OCD symptoms	LEVEL 2—Repetitive Thoughts and Behaviors—Adult (adapted from the Florida Obsessive-Compulsive Inventory [FOCI] Severity Scale [Part B])	X	X	X
		Distress severity for specific fears	Self-report	X	X	X
	**Depression**					
		Depression symptoms	Depression Anxiety Stress Scales (DASS21)	X	X	X
	**Behavioral measures**					
		Alcohol consumption	Self-report	X	X	X
		Help seeking	Self-report	X	X	X
		Medications	Self-report	X	X	X
	**Functional measures**					
		Sleep	Insomnia Severity Index (ISI)	X	X	X
		Difficulties with emotions and relationships	Strengths and Difficulties Questionnaire (SDQ)	X	X	X
		Satisfaction with social roles	PROMIS Satisfaction with Social Roles and Activities measure	X	X	X
		Nonspecific distress	Kessler Distress Measure (K10)	X	X	X
		Confidence in ability to manage anxiety symptoms	General Perceived Self-efficacy Scale (GSE)	X	X	X
		Motivation to work on anxiety	Self-report	X	X	X
	**Process measures**					
		Program use and engagement	Self-report		X	
		Usefulness of GAD Online or Lantern	Self-report		X	
		Satisfaction with GAD Online or Lantern	Client Satisfaction Questionnaire (CSQ)		X	

#### Repetitive Thoughts and Behaviors

The LEVEL 2—Repetitive Thoughts and Behaviors—Adult (adapted from the Florida Obsessive-Compulsive Inventory [FOCI] Severity Scale [Part B]) [59] assesses obsessive-compulsive disorder symptoms. This emerging measure of the DSM-V was developed to be administered at the initial patient interview and to monitor treatment progress.

#### Depression Anxiety Stress Scales-Short Form

The Depression Anxiety Stress Scales-Short Form (DASS21) [60] is a 21-item self-report measure designed to measure negative emotional states of depression, anxiety, and tension or stress. The DASS is divided into 3 self-report scales. The depression scale assesses dysphoria, hopelessness, devaluation of life, self-deprecation, lack of interest/involvement, anhedonia, and inertia. The Anxiety Scale assesses autonomic arousal, skeletal muscle effects, situational anxiety, and subjective experience of anxious affect. The Stress Scale is sensitive to levels of chronic nonspecific arousal, assessing difficulty relaxing, nervous arousal, and being easily upset/agitated, irritable/over-reactive, and impatient. All scales have been shown to have high internal consistency and to yield meaningful discriminations in a variety of settings.

#### Insomnia Severity Index

The Insomnia Severity Index is a 7-item self-report questionnaire to assess insomnia severity [61]. It has adequate internal consistency and is a reliable self-report measure to evaluate perceived sleep difficulties. This measure, along with the other measures of general functioning, was included to assess the impact of the active interventions on functional impairments typically associated with GAD.

#### Strengths and Difficulties Questionnaire

The Strengths and Difficulties Questionnaire [62] assesses self-reported difficulties with emotions, concentration, and relationships. It is a reliable short-form, self-report assessment of inattention, peer relationships, and pro-social behavior, factors that, if improved, could indicate positive impact of the active interventions.

#### Satisfaction With Social Roles

The PROMIS Satisfaction with Social Roles and Activities measure [63] is an 8-item self-report assessment of satisfaction with one’s ability to perform daily activities and meet the needs of various relationships.

#### Kessler Distress Measure

The Kessler Distress Measure [64] assesses nonspecific distress. The 10-question (K10) self-report scale has good precision as well as consistent psychometric properties across major sociodemographic subsamples. This measure was included as an assessment of a global outcome of reduced general distress.

#### General Perceived Self-Efficacy Scale

The General Perceived Self-Efficacy scale (GSE) [65] is a 10-item self-report measure that assesses beliefs in one’s capability to handle new and difficult tasks and adaptive challenges after experiencing stressful life events. This measure was included because enhanced self-efficacy is considered one of the main psychological benefits of self-help interventions [66].

### Program Use and Engagement

Program usage will be examined for the 2 active intervention groups with respect to 3 indices: frequency of logins, frequency of self-monitoring, and number of modules accessed. Reason for drop out will be assessed via self-report questions in the survey as well as a semistructured interview with those who are willing to enroll in a follow-up substudy. For both the GAD Online and Lantern platforms, module access can be passively monitored. Engagement in Lantern can be further qualified in terms of engagement with the program coach. The Lantern software can program reminders for coaches to reach out to inactive users after a specific period. Coaches are given training in motivational interviewing and encouraged to use these skills to help engage users and address fluctuating stages of change during the intervention. Unstructured data (ie, text) from users’ program entries and correspondence with coaches can be qualitatively (eg, language used) and quantitatively (eg, user: coach message frequency) evaluated, with participant consent and understanding that message content can be used for research, to examine motivational strategies and engagement.

### Program Satisfaction

Program satisfaction will be examined for the 2 active intervention groups using the Client Satisfaction Questionnaire (CSQ) [67]. The CSQ is an 8-item self-report statement of satisfaction with health and human services. The generic questionnaire has been customized for each intervention (eg, replacing the term “service” with “the GAD Online program” or “the Lantern Anxiety Program”). Those using Lantern will also provide feedback on their experience working with the program coach.

### Data Management

All data will be stored on secure servers hosted by Qualtrics, and data downloaded from those servers will be managed and stored on encrypted computers accessed only by members of the Stanford research team.

### Analysis

#### Descriptive Analyses

Chi-squares (categorical variables) and *t* tests (continuous variables) will be used to compare demographic variables and baseline scores on the outcome measures for the 3 groups. Findings will be reported according to the CONSORT guidelines [68], including a trial flowchart. This will include total students assessed for inclusion and exclusion criteria within period of screening, number of students meeting inclusion or exclusion criteria, number screened for eligibility, number agreeing to enter the intervention trial, and number refusing or excluded (with reasons). The number continuing through the trial, actively withdrawing, and passively lost to follow-up will be shown by arm. The outcome measures will be summarized at baseline/screening, at 3-month and 9-month follow-up by the intervention arm and overall.

#### Outcome Analyses

A 3 condition × time mixed-design ANOVA will be conducted to examine both primary and secondary hypotheses. Using a mixed-design ANOVA will test for differences between 2 or more independent groups while subjecting participants to repeated measures. The model is a type of mixed effect model, with the fixed effects factor being a between-subjects variable and the random effects factor being a within-subjects variable. Follow-up paired comparisons will be conducted to specifically assess if there is significant differential change in GAD symptoms between each active condition and control from the baseline to the postcondition and follow-up assessments. Within- and between-group effect sizes will be calculated using Cohen’s *d* (based on the pooled standard deviation), specifically contrasting each active condition with the control condition for the main outcome.

Primary analyses will be undertaken using an intention-to-treat (ITT) approach, including all participants randomized regardless of treatment actually received, program engagement, or withdrawal from the trial. Using a mixed model design will allow us to include participants with missing data, which is likely to occur in large Internet-based trials.

Study site will be included as a covariate as this might have an influential effect given that the 3 sites were selected primarily based on accessibility versus between-site comparability. If some sites have poor recruitment, the data will be combined.

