### Design

A parallel arm, 3 (condition) × 3 (time) randomized controlled trial with equal allocation of students between arms will be used. Students will be randomized to the unguided GAD Online intervention, the guided Lantern intervention, or a wait-list control group. Those assigned to the GAD Online or Lantern group will have full program access for 3 months. Outcomes will be assessed at screening/baseline, postintervention (3 months), and 6-month follow-up (9 months).

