#### Eligibility

Eligible participants will be current students of the colleges, all of which are English medium, aged 18 or older who provide their email address, informed consent to complete the study, and meet criteria for clinical or subthreshold GAD. This age range was chosen because individuals younger than 18 require parental consent for participation in research. Based on self-report responses in the online survey, students are categorized into clinical, subthreshold, and asymptomatic for GAD. Those who meet DSM-V diagnostic criteria for GAD as measured by criterion-based scoring of the 4th edition of the Generalized Anxiety Disorder Questionnaire (GAD-Q-IV) [42] are classified as clinical, or more realistically,

“a probable diagnosis of GAD based on self-report.” To note, the diagnostic criteria did not change from DSM-IV to DSM-V, and therefore the GAD-Q-IV questions can still be used to assess DSM-V GAD criteria. Those who score 5.7 or above using dimensional scoring of the GAD-Q-IV but are not clinical are classified as “subthreshold.” All others are asymptomatic. It is also important to note that clinical diagnosis should be established using a clinical interview, which is not feasible in this study, thus the use of the self-report measures. Moreover, this study’s aim is not to provide diagnoses to students but rather to use gold-standard instruments to provide appropriate “matches” between students and available resources (ie, the research study or referral).

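### Read classically, the mixed-design ANOVA assumes equal variance for the 0-3, 3-9 and 0-9 month changes, which this design makes unlikely; the month-3 and month-9 contrasts should each carry their own standard error

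*Protocol article*

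**What the plan says.** Outcome Analyses in the protocol article names the method: "A 3 condition × time mixed-design ANOVA will be conducted to examine both primary and secondary hypotheses". It gives the purpose of the method: "Using a mixed-design ANOVA will test for differences between 2 or more independent groups while subjecting participants to repeated measures". It describes this as a type of mixed effect model, "with the fixed effects factor being a between-subjects variable and the random effects factor being a within-subjects variable". The comparisons that answer the trial's question come next: "Follow-up paired comparisons will be conducted to specifically assess if there is significant differential change in GAD symptoms between each active condition and control", taken from baseline to the month-3 and the month-9 assessments. The section adds: "Using a mixed model design will allow us to include participants with missing data". It states no covariance structure, no sphericity correction and no error term for the follow-up comparisons.

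Three design features bear on this. The Design section places assessments at 0, 3 and 9 months. Under Baseline Assessments, the baseline survey doubles as the eligibility screen. Under Eligibility, entry is defined on the GAD-Q-IV, which is also the primary outcome: students are either clinical by criterion-based scoring or subthreshold, the latter being "Those who score 5.7 or above using dimensional scoring of the GAD-Q-IV but are not clinical". Under Measures, month 3 is the primary end point and month 9 shows whether the effect is sustained.

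**The concern.** A classical mixed-design ANOVA has one subject-by-time error term. A contrast of change between two visits that uses this term has a correct standard error only if all pairwise changes have the same variance. Two features of this design work against that. The gaps are 3, 6 and 9 months, and correlations between scores often differ with the length of the gap. Entry at a minimum score also narrows the spread of the baseline GAD-Q-IV relative to later visits.

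With unequal change variances, the common error averages over them. Some contrasts then get a standard error that is too wide and lose power; others get one that is too narrow and reject too often. The problem exists with complete data, so it is separate from the handling of missing surveys. A sphericity correction of the overall F test would not repair the individual contrasts. The contrasts affected are the primary one at month 3 and the sustainability one at month 9.

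**Working it through.** **The plan's own figure.** Sample Size Estimation gives d = 1.73/3.46 = 0.5, 80% power and a 5% level. The normal formula gives n = 2 × (1.96 + 0.84)² / 0.5² ≈ 63 per group, and the t-based formula gives 63.8, so the stated 64 reproduces. A target of 100 with 30% loss leaves 70 per group, with power of about 84%.

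**Inputs from the article.** Visits at 0, 3 and 9 months (Design). Share meeting entry criteria in the pilot survey: 8/78 + 17/78 = 25/78, or 32% (Preliminary Feasibility and Acceptability Evaluation).

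**Assumptions.** The between-visit correlations r03, r39 and r09 are not in the article, so I vary them. Scores have equal variance (set to 1) at every visit before selection. The entry cut is approximated as keeping the top 25/78 of a normal baseline score. That cut has z = 0.466 and selected mean λ = 1.116, so baseline variance falls to k = 1 + 0.466 × 1.116 − 1.116² ≈ 0.274 of its unselected value.

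**Formulas.** After selection on baseline:
- V03 = 2(1 − r03) − (1 − k)(1 − r03)²
- V09 = 2(1 − r09) − (1 − k)(1 − r09)²
- V39 = 2(1 − r39) − (1 − k)(r03 − r09)²

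Without the cut, k = 1 and the last terms vanish. The common error corresponds to P = (V03 + V39 + V09)/3. The ratio of common-error to true standard error is √(P/V03) at month 3 and √(P/V09) at month 9.

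**Worked case.** With r03/r39/r09 = 0.7/0.6/0.5 and no cut, V03 = 0.6, V39 = 0.8 and V09 = 1.0, so P = 0.8. The month-3 ratio is √(0.8/0.6) = 1.155 and the month-9 ratio is √(0.8/1.0) = 0.894.

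| r03/r39/r09 | Month 3, no cut / cut | Month 9, no cut / cut |
|---|---|---|
| Decay 0.8/0.8/0.7 | 1.080 / 1.080 | 0.882 / 0.900 |
| Decay 0.7/0.7/0.5 | 1.106 / 1.095 | 0.856 / 0.885 |
| Decay 0.7/0.6/0.5 | 1.155 / 1.151 | 0.894 / 0.930 |
| Stable after month 3: 0.5/0.8/0.45 | 0.913 / 0.924 | 0.870 / 0.891 |
| Equal 0.3 | 1.000 / 1.055 | 1.000 / 1.055 |
| Equal 0.5 | 1.000 / 1.036 | 1.000 / 1.036 |
| Equal 0.6 | 1.000 / 1.028 | 1.000 / 1.028 |

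**Consequences if the common error is used.** Type I error is 2(1 − Φ(1.96 × ratio)).
- In the three decay rows, the month-9 ratios of 0.856 to 0.930 give 9.3% down to 6.8%. Month-3 power for a contrast with 80% under its own standard error is Φ(2.80 − 1.96 × ratio): 75% at 1.080 and 70% at 1.155. Starting from 70 per group, the corresponding figures are 80% and 76%.
- In the stable row, type I error is about 7% at month 3 and 8-9% at month 9.

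**Simulation check.** Null data, 100 per arm, complete follow-up, with the entry cut, 4,000 runs. With the common error, rejection at month 3 / month 9 was 0.026 / 0.065 for 0.7/0.6/0.5, 0.074 / 0.079 for the stable case and 0.050 / 0.046 for equal 0.5. With each contrast's own error it was 0.047-0.058 in every scenario run.

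**How far the direction can be fixed.** Over a grid of correlations from 0.20 to 0.90 with r09 ≤ r03 and the cut applied, 872 of 1,678 cases had month 3 too wide and month 9 too narrow, 503 had both too wide and 303 had both too narrow. Requiring also that correlation never rises with a longer gap (r03 ≥ r39 ≥ r09) gave 560 of 634 with the mixed pattern and 74 with both too wide.

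**The case against.** The strongest reply is that the article never says one error term is pooled over visits for the follow-up comparisons. It calls the analysis a mixed model that keeps incomplete participants, which suggests a likelihood-based fit in which the covariance is a detail for the analysis plan. A comparison of change scores between two arms, each with its own variance, would be calibrated. This stands in part: the miscalibration is conditional on the common error being used. But the article does name a method, with a single random within-subjects factor, and presents the contrasts as follow-ups to it. The usual reading of that method carries the equal-variance assumption, and keeping participants with missing data does not relax it.

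A reader might infer that the month-3 interval is certainly too wide and the month-9 interval certainly too narrow. The article does not support this, because it gives no between-visit correlations. An intervention that ends at month 3 could plausibly leave scores stable afterwards, and then both intervals are too narrow.

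A reader might also blame the entry cut for the month-9 narrowing. It works the other way: for 0.7/0.7/0.5 the month-9 ratio is 0.856 without the cut and 0.885 with it. Nor is the error negligible whenever correlations are equal: with the cut it is 3.6% at 0.5 and 5.5% at 0.3.

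Finally, the power loss under decay is cushioned by the target of 100 per arm, and there the primary contrast errs on the conservative side. Both points are fair. Neither covers the stable case, where the primary contrast is anti-conservative.

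**Conclusion.** The concern holds in conditional form. The named ANOVA, read classically, assumes a common variance of change that the visit spacing and the restricted baseline make unlikely. If the follow-up contrasts use that error:
- under the decay patterns tried, the month-3 standard error is about 8-16% too wide and the month-9 one about 7-14% too narrow, with month-9 type I error of about 7-9%;
- with stability after month 3, both are about 8-13% too narrow;
- with equal correlations of 0.3-0.6 and the entry cut, both are about 3-6% too wide.

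These sizes rest on assumed correlations, a normal score cut at the pilot share, equal variances at each visit before selection, and the same covariance in each arm. The direction cannot be settled from the article, and a pooled error for the contrasts is implied by the method's name rather than stated. The matter merits a clarification of the analysis; it does not show that a planned result will be wrong.

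**What to change.** State in Outcome Analyses that the month-3 and month-9 contrasts of each active arm against control come from one of two models:
- a likelihood-based repeated-measures model for the GAD-Q-IV with condition, visit and their interaction, and an unstructured 3 × 3 covariance; or
- a separate model at each visit, adjusted for baseline GAD-Q-IV.

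Either gives each contrast its own standard error, whichever way the correlations fall. The first also serves the stated aim of including participants with missing data. The site covariate can stay as planned. If the analysis plan already specifies one of these, a sentence in the protocol saying so is enough. The cost is one line of specification; the unstructured model has six covariance parameters, which 300 students can readily support. No new data are needed.

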**Methods:**

Students will be recruited via 3 colleges in Hyderabad, India, and referred for a campus-wide online screening. Self-report data will be collected entirely online. A total of 300 qualifying students will be randomized in a 1:1:1 ratio to receive GAD Online, Lantern, or to be in a wait-list control condition, stratified by clinical and subthreshold GAD symptomatology. Students will complete a postintervention assessment after 3 months and a follow-up assessment 6 months later, at which point students in the wait-list control condition will receive one of the programs. The primary outcome is GAD symptom severity at 3 months postintervention. Secondary outcomes include GAD caseness at 9 months, other anxiety and depression symptoms, self-efficacy, and functional measures (eg, sleep, social functioning) at 3 and 9 months, respectively. Primary analyses will be differences between each of the intervention groups and the wait-list control group, analyzed on an intention-to-treat (ITT) basis using mixed-design ANOVA.

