#### Sample Size Estimation

The sample size estimation is based on detecting differences in GAD symptom severity change (measured using dimensional scoring of the GAD-Q-IV) from baseline to post- and follow-up assessments between each active conditions and the wait-list control group. Treatment trials of online, CBT-based, guided self-help interventions for GAD have found an average large effect size of roughly 1.07 relative to a wait-list control group using the GAD-Q-IV [38]. In this study, more than half of the treated participants had recovered according to a structured interview, suggesting that a treatment effect size of 1.07 is clinically meaningful. Treatment trials of purely self-help interventions for subthreshold and clinical anxiety have found smaller yet still promising effect sizes ranging from 0.62 to 0.84, respectively, relative to a wait-list control group [31].

To enable detection of difference in mean change between each active intervention and the control group, the sample size is powered to detect at least a medium effect size of 0.5. With 80% power and assuming a 5% significance level, a minimum total sample size per group of 64 is required. Assuming the GAD-Q-IV SD is 3.46 [49], the proposed sample size provides 80% power to detect a between-group effect corresponding to a GAD-Q-IV change of 1.73 points (or a Cohen’s *d* of 0.5 or greater). By targeting 100 students recruited per condition (N=300), even allowing for nearly 30% attrition, which is a possibility in Internet-based intervention trials, GAD-Q-IV mean differences between each active condition compared with the wait-list control condition will be detected with sufficient power. The difference in mean change between the two active conditions is not a primary comparison, as they are two different programs.

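### The primary analysis is named as a mixed-design ANOVA, credited with a likelihood-based mixed model's handling of missing surveys, and described with time as the random factor

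*Protocol article*

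**What the plan says.** The abstract (Methods) states that the primary comparisons of each intervention with the wait-list will be "analyzed on an intention-to-treat (ITT) basis using mixed-design ANOVA". It names no other model. Outcome Analyses repeats the mixed-design ANOVA for the primary and secondary hypotheses. It classes this as a kind of mixed effect model, "with the fixed effects factor being a between-subjects variable and the random effects factor being a within-subjects variable". It then promises an intention-to-treat analysis of everyone randomized, whatever their engagement or withdrawal, and adds: "Using a mixed model design will allow us to include participants with missing data". Follow-up comparisons of each active arm with control are planned for change from baseline to both later assessments.

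The Design section describes three conditions by three times, with surveys at baseline, 3 months and 9 months. The Measures section makes 3 months the primary end point. Sample Size Estimation requires 64 per group and recruits 100 per group, so that power is sufficient "even allowing for nearly 30% attrition". It does not say at which survey that attrition is counted.

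**The concern.** Two different methods are treated as one. A mixed-design (split-plot, repeated-measures) ANOVA in its standard form needs a value at every level of the within-subject factor and deletes incomplete students listwise. A linear mixed model fitted by likelihood uses whatever observations each student has. The protocol names the first and claims the missing-data behaviour of the second.

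The description of the factors does not settle which is meant, because it is wrong for either. The three visits are chosen time points, and the effect of interest is differential change at a particular one of them. Time and condition-by-time therefore have to be fixed, and the student is the random unit.

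What is at stake is who contributes to the month-3 result. Under listwise deletion, a student with a valid 3-month score leaves the primary analysis for not answering six months later. The protocol gives some reason to think 9-month response could differ by arm. Wait-list students receive a program only after completing the later surveys, whereas students in the active arms lose access at month 3. Students who still meet clinical criteria at the end of the intervention are referred elsewhere, so later response could also depend on the 3-month score. Two analysts following the same section could analyse different samples.

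**Working it through.** **Inputs from Sample Size Estimation.** Effect size 0.5, SD 3.46, difference 1.73 points, 5% significance (two-sided assumed, as the text does not say), 80% power, 100 recruited per arm, nearly 30% attrition.

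**1. Reproduce the plan's figure.** n per group = 2(1.96 + 0.84)² / 0.5² = 2 × 7.85 / 0.25 = 62.8, so 63 by the normal approximation. The two-sample t test gives 63.8, so 64. The plan's 64 reproduces. To retain 64 after 30% loss, 64 / 0.70 = 91.4, so 92 must be recruited; 100 covers this.

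**2. Power if every incomplete student is dropped and 30% is the total loss.** 100 × 0.70 = 70 per arm. Power ≈ Φ(0.5 × √(70/2) − 1.96) = Φ(2.96 − 1.96) = Φ(1.00) = 84.1%; the t test gives 83.6%. So the plan's power survives even a complete-case analysis on this reading.

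**3. Where power would fall short.** 64 completers out of 100 is a 36% loss. If 30% is instead the loss at month 3, the further loss by month 9 that brings 70 down to 64 is 1 − 64/70 = 8.6%. The plan gives no figure for further loss, so the range below is an assumption (t test, two-sided 5%, d = 0.5).

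| Further loss among the 70 | Complete cases per arm | Power |
|---|---|---|
| 0% | 70 | 83.6% |
| 10% | 63 | 79.5% |
| 20% | 56 | 74.6% |
| 30% | 49 | 68.8% |

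A month-3 comparison using all 70 students with a 3-month survey keeps about 84% power whatever happens at month 9.

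**4. Possible bias in the month-3 contrast (illustration).** Assume no true effect, SD 3.46 at each time and a baseline-to-3-month correlation of 0.5. In one active arm, let 9-month loss be 35% among students above the 3-month median and 5% among those below (20% on average). In the control arm, let it be 20% regardless of score. In a normal distribution the two halves have means of ±0.798 SD.

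- Shift in the retained 3-month mean in that arm: 3.46 × 0.798 × (0.65 − 0.95) / (0.65 + 0.95) = 3.46 × 0.798 × (−0.1875) = −0.52 points.
- The retained baseline mean shifts by half of that (correlation 0.5), so the shift in change from baseline is −0.52 × (1 − 0.5) = −0.26 points, about a quarter of a point.
- Relative to the target: 0.26 / 1.73 = 15%.

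Using all 3-month values, the shift under this pattern is about zero, because the loss occurs after the 3-month score is observed.

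**5. The random-factor description.** Set beside the Design and Measures sections, the within-subjects variable is time at 0, 3 and 9 months, and the primary question concerns month 3 specifically. A factor whose individual levels are the target of inference is fixed. No section names the student as the random effect or mentions likelihood estimation.

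**The case against.** The strongest reply is that Outcome Analyses states its intention plainly. It calls the model a mixed effect model, puts all randomized students in the analysis set, and says those with missing data will be included. No section plans listwise deletion. This stands. A reader might infer that the protocol intends a completers analysis, and the text does not support that. The deletion follows from the named method, not from a stated plan. What remains is that the named method does not do what the section says it does.

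A reader might also infer that the promised power fails. On the plan's own figures it does not: step 2 gives about 84% in the worst case if 30% is total loss. The sample size text refers to change to both later assessments, so reading the 30% as an overall figure is natural.

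A third inference would be that a random time factor leaves the treatment test with very few denominator degrees of freedom. That applies to the condition main effect averaged over visits. The trial's question is condition-by-time, to which that argument does not apply.

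The follow-up comparisons from baseline to post-intervention could be run on every student with a 3-month survey, so loss of those students from the key contrast is possible but not certain. The bias figure rests on an assumed dropout pattern, not on anything the protocol reports. Finally, a condensed article may leave covariance details to an analysis plan. That is fair, but the model's name and the role of time are stated here, and stated wrongly.

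**Conclusion.** The point holds as an error in how the primary analysis is named and described. The abstract and Outcome Analyses name a method that in standard form drops incomplete students, credit it with keeping them, and assign the random effect to the wrong factor. If the analysis is run as named over three surveys, the month-3 result would be conditional on answering at month 9, contrary to the stated intention-to-treat set.

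The size of the consequence is conditional. Bias of about a quarter of a point (15% of the target difference) is an illustration that requires listwise deletion and strongly score-dependent 9-month loss in one arm only. Power below 80% requires more than about 36% of students to lack a complete set of surveys, for example 30% lost by month 3 and a further 10% by month 9. Neither pattern is given in the plan, and neither is a demonstrated result. The power figures also take 3.46 as the SD of the analysed quantity, as the plan does; for a change score, that equality needs a baseline-to-follow-up correlation of 0.5.

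**What to change.** In the abstract and in Outcome Analyses, replace the mixed-design ANOVA with a likelihood-based linear mixed model for repeated measures, using all available observations from every randomized student. Specify condition, categorical time (0, 3, 9 months) and condition-by-time as fixed effects, keep study site as the covariate already planned, and model within-student correlation by a random student effect or an unstructured covariance. State that each active-minus-wait-list contrast at month 3 is the primary estimate. Delete the description that makes the within-subjects variable the random factor. State that the analysis assumes data are missing at random. In Sample Size Estimation, it would help to say whether the 30% attrition is counted at month 3 or in total by month 9.

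The cost is wording and different analysis code. No new data, visits or participants are needed.
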